In our preclinical work, vitamin C supplementation lowered inflammatory markers, mortality, and pancreatic necrosis in SAP mice (15, 16). Whether this carries over to humans is unclear. Existing clinical data are inconsistent and come from small samples, insufficient dosing, or cohorts weighted toward mild disease (17). From September 2019 to December 2023, we conducted a single-center, double-blind, randomized, placebo-controlled trial (ChiCTR1900022022) investigating HDIVC (200 mg/kg/24 h, 1 g/h, for 7 days) (6). The primary outcome of 28-day mortality did not differ significantly between treatment groups in the overall cohort (*n* = 212). However, prespecified subgroup analysis revealed that MSAP patients receiving HDIVC demonstrated significant reductions in C-reactive protein levels and improved fluid balance. These findings suggest HDIVC may attenuate inflammatory responses in MSAP, though its therapeutic value in SAP requires confirmation through adequately powered multicenter randomized controlled trials. Extensive preclinical investigations over the past few decades have established the therapeutic potential of HDIVC in SAP, with mechanistic understanding progressively refined through cellular, animal, and early-phase human studies. While these foundational studies show biological plausibility, current clinical evidence remains limited to underpowered single-center trials, precluding definitive conclusions about therapeutic efficacy. To address this critical evidence gap, we propose a multicenter, prospective, randomized, double-blind, placebo-controlled trial evaluating early HDIVC administration (500 mg/kg/day for 7 days, 2 g/h) in SAP patients. The primary outcome is organ support-free days (OSFD) within the first 14 days. Secondary outcomes include ICU all-cause mortality, inflammatory biomarker, organ failure scores and fluid retention. This study aims to determine whether HDIVC represents a clinically meaningful, cost-effective therapeutic intervention capable of improving outcomes in this high-mortality condition, with potential to inform future guideline recommendations.

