## Method and analysis

### Study design

This prospective, randomized, double-blind, multicenter trial will investigate whether early intravenous HDIVC reduces OSFD within the first 14 days in SAP patients. We will enroll 238 participants (119 per group) from eight hospitals across China, with block randomization allocating patients to either HDIVC or control groups. Serial assessments of organ function, disease severity scores, and mortality will be evaluated at predefined time points before and after treatment to determine therapeutic efficacy. The evaluation and examination will be continued from randomization to 180 days or death. Figure 1 shows the flow chart of the study. This study protocol is written according to the Standard Protocol Items for Randomization Trials (SPIRIT) statement (18).

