### Eligibility criteria

#### Inclusion criteria

Participants must meet the following criteria:

Age ≥ 18 years;Time from onset to enrollment is less than 7 days;Meets the diagnostic criteria for SAP per the 2012 Atlanta Guidelines, defined by persistent organ failure (modified Marshall score of 2 or higher lasting more than 48 h). Confirmation of the 48-h persistence must be completed within 7 days of disease onset.

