### Secondary outcome

The secondary outcomes are: (1) ICU all-cause mortality, defined as death from any cause from randomization to ICU discharge or transfer. (2) Early SAP inflammatory markers, including C-reactive protein and cytokines IL-6, IL-1, and IL-10. (3) Organ function scores, including SOFA and modified Marshall scores. (4) Fluid retention. (5) Disease severity scores, including APACHE II and BISAP scores. (6) Pancreatic necrosis measured by CTSI scores. (7) Other prognostic indicators including the incidence of infected pancreatic necrosis, ICU length of stay, and hospitalization costs. (8) Plasma vitamin C concentrations before and after treatment. (9) Adverse events related to vitamin C. (10) Gut microbiota composition.

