### Statistical methods

The statistical analysis will follow an intention-to-treat (ITT), per-protocol (PP), and safety population approach. All statistical tests will be two-sided, with a *p*-value < 0.05 considered statistically significant. Baseline characteristics will be summarized using descriptive statistics. For quantitative variables, descriptive statistics will include calculations of mean, standard deviation, median, minimum, maximum, and interquartile range (IQR). For categorical variables, descriptive statistics will report frequencies and percentages for each category.

The primary outcome, OSFD within the first 14 days, will be analyzed using a linear mixed-effects model with center included as a random intercept, allowing quantification and adjustment for between-center variability. Sensitivity analyses will treat center as a fixed effect or omit center effects to assess robustness. A treatment-by-center interaction test will be performed to evaluate heterogeneity of treatment effect across sites. The intraclass correlation coefficient (ICC) from the null model will be reported. To control the familywise type I error rate for secondary outcomes, a hierarchical (fixed-sequence) testing procedure is applied. The pre-specified order is: (1) ICU all-cause mortality, (2) SOFA score at Day 7, (3) C-reactive protein at Day 7, (4) APACHE II score at Day 7, followed by all remaining secondary outcomes. Each outcome is formally tested only if all preceding outcomes in the hierarchy reach statistical significance at the two-sided *α* = 0.05 level. Outcomes below the hierarchical chain—including cytokine levels (IL-6, IL-1, IL-10), BISAP score, CTSI score, ICU length of stay, hospitalization costs, and gut microbiota composition—are designated as exploratory. Their *p*-values will be reported descriptively without formal inferential claims.

Bioinformatics processing will use QIIME2 with DADA2 denoising to generate amplicon sequence variants (ASVs), and taxonomic assignment will be performed against the SILVA database. Alpha diversity (Shannon, Chao1 indices) will be compared between groups using Wilcoxon rank-sum tests. Beta diversity (Bray-Curtis, UniFrac distances) will be visualized by principal coordinate analysis (PCoA) and tested by PERMANOVA. Differential abundance analysis will be conducted using LEfSe (LDA > 2.0) and MaAsLin2. Longitudinal changes will be analyzed using linear mixed-effects models if serial samples are available.

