HDIVC represents a promising adjunctive therapy for SAP by targeting oxidative stress and systemic inflammation. If proven effective, the study may provide evidence to support future guidelines. However, several challenges still remain. Patient heterogeneity and variability in disease course may influence treatment response. Patients >100 kg are excluded because weight-based dosing in predominantly adipose excess could yield a disproportionately high drug load. The 50 g/d cap is consistent with established safety limits (21), though this limits generalizability to obese SAP patients. Inter-center variability in supportive care is inevitable in a pragmatic eight-center trial. We mitigate this through centralized training, protocol-driven management, including center as a random intercept, and prospectively recording concomitant therapies. Timely enrollment is critical to capture the early inflammatory phase, but in clinical practice, delays in diagnosis or transfer may limit early intervention. To avoid this as far as possible, we set a 7-day cutoff from the onset of the disease during which vitamin C may exert therapeutic effect on SAP. But the 7-day enrollment window requires organ failure documentation by Day 5 to meet the Atlanta SAP criteria, which may delay or preclude enrollment.

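### Timing is central to the trial's rationale, yet treatment can span Days 2–9 to about Days 7–14 from onset, the 7-day window is ambiguous, and no named stratum or model term uses time from onset

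*Protocol article*

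**What the plan says.** - **Aim.** The Introduction announces a "trial evaluating early HDIVC administration (500 mg/kg/day for 7 days, 2 g/h) in SAP patients". Study design repeats the word *early*.
- **Entry.** Inclusion criteria set "Time from onset to enrollment is less than 7 days" and require "persistent organ failure (modified Marshall score of 2 or higher lasting more than 48 h", with persistence confirmed inside the same 7 days.
- **Treatment length.** Intervention fixes seven consecutive days, in cycles that run from 06:00 to 06:00.
- **Role of timing.** The Discussion lists timing among the factors that decide whether vitamin C works. It stresses prompt enrolment so as to catch the early inflammatory phase, and then states: "we set a 7-day cutoff from the onset of the disease during which vitamin C may exert therapeutic effect on SAP". It next calls the same seven days an enrolment window. It concedes that the organ-failure criterion can delay or prevent entry.
- **Analysis.** Randomization stratifies by centre and etiology. In Statistical methods, the primary OSFD model has a random intercept for centre, and its sensitivity analyses vary only how centre is handled. Subgroup interaction tests are promised for severity and for baseline variables that are not listed.
- **Inflammatory markers.** The secondary outcomes include "Early SAP inflammatory markers, including C-reactive protein and cytokines IL-6, IL-1, and IL-10". The fixed testing sequence begins "1) ICU all-cause mortality, (2) SOFA score at Day 7, (3) C-reactive protein at Day 7", so Day 7 CRP is the only one of these markers with a named place in it.

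**The concern.** The 7-day limit applies to enrolment, while treatment lasts a further seven days. If the Discussion sentence describes when the drug can act, part of every patient's course falls after that period. If it describes the latest time to enrol, patients treated from Day 2 and from almost Day 7 are both called early, although their starts differ by nearly five days. On either reading the trial averages over a wide range of disease time.

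The interpretation of the result is at stake. If benefit depends on delay, one average cannot show how. A null average would not exclude benefit from prompt treatment, and a positive one would not by itself show benefit near Day 7. Time from onset has to be established for every patient to check eligibility, so leaving it out of the named analyses gives up information that the trial already holds.

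**Working it through.** **The article's own figures.** The Discussion says that organ failure must be documented by Day 5. This follows from the entry rule: 7 days − 48 h = 5 days. The article gives no figure for the share of infusion inside the 7-day window. Its sample size also reproduces: 2 × [5 × (1.960 + 0.842)/2]² = 98.1; 98 × 1.15 = 112.7, so 113; 113/0.95 = 118.9, so 119 per group and 238 in total.

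**Inputs.** Earliest entry is just after Day 2 and latest just before Day 7 (Inclusion criteria). The infusion lasts 7 days (Intervention). The window is 7 days from onset (Discussion). The calculation assumes that infusion starts at entry and is spread evenly over the seven days.

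**Span of treatment.** For a start at day d from onset, infusion ends at d + 7: Day 9 for d = 2, and about Day 14 for d just under 7. Study Day 7, when CRP is tested, falls at the same disease times.

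**Share after Day 7.** Inside = (7 − d)/7; outside = d/7.

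| Start (days from onset) | Inside | Outside |
|---|---|---|
| 2 | 71% | 29% |
| 3 | 57% | 43% |
| 3.5 | 50% | 50% |
| 4 | 43% | 57% |
| 5 | 29% | 71% |
| 6 | 14% | 86% |
| just under 7 | about 0% | about 100% |

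The entry rule alone guarantees 2/7 = 29% outside. More than half falls outside only if d > 3.5.

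**Average over patients.** The article gives no distribution of entry times, so these are assumptions. For uniform entry on [a, b] the mean outside is (a + b)/14, and the proportion of patients with more than half outside is (b − 3.5)/(b − a).

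| Assumed entry | Mean outside | Patients with more than half outside |
|---|---|---|
| Days 2–7 | 4.5/7 = 64% | 3.5/5 = 70% |
| Days 2–5 | 3.5/7 = 50% | 1.5/3 = 50% |
| Days 2–4 | 3/7 = 43% | 0.5/2 = 25% |

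If the first infusion also waited a full 24 h for the 06:00 start (a further assumption), the means become 77%, 64% and 57%, and the proportions 90%, 83% and 75%.

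**Precision of an interaction with time from onset.** Take SD 5 and 113 evaluable patients per group. The standard error of the difference in slopes is 5 × √2/(√113 × SD of entry time).
- Uniform entry over Days 2–7: SD = 5/√12 = 1.443, SE = 7.071/(10.63 × 1.443) = 0.46, 95% half-width 1.96 × 0.46 = 0.90 OSFD per day of delay.
- Uniform entry over Days 2–4: SD = 2/√12 = 0.577, SE = 1.15, half-width 2.3 OSFD per day of delay.

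The planned main effect is 2 days, so this interaction can describe a trend but cannot confirm one.

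**The case against.** A reader might infer that most of the infusion is given outside an active period. The documents do not support that. The 48-h rule and the 7-day course guarantee only 2 of 7 days after Day 7; *most* needs a start after Day 3.5, and no entry-time distribution is given. The Discussion sentence also sits among remarks on timely enrolment and is followed by a reference to an enrolment window. Nothing says that infusion after Day 7 is inactive or must stop. This part of the objection stands.

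A reader might also infer that the objective goes unanswered whatever the result. That does not follow. Randomisation balances time from onset between arms in expectation, so the ITT contrast is a valid average for the patients enrolled. Averaging over an entry window is ordinary design, and the article does not argue for a gradient of benefit within the seven days. It also partly discloses the delay.

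The unlisted baseline variables for subgroups might include time from onset, and an analysis plan that is not shown could name it. That limits the claim to what the article names. But the article does not leave all adjustment to a later document: it specifies the primary model and its sensitivity analyses, and it commits to adjusting for CRRT parameters and concomitant therapies. Time from onset is named in none of these, although the Discussion treats timing as decisive.

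Preferring Day 3 over Day 7 CRP would be a matter of taste. A spread in disease time that is common to both arms does not bias the contrast.

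**Conclusion.** The point holds in limited form. Infusion extends beyond Day 7 from onset for every patient: at least 2 of 7 days, and more than half for any start after Day 3.5. The average lies between 43% and 64% under the uniform entry patterns tried without a start lag, and reaches 77% with a 24-h lag. These shares matter only if the 7-day period means the time in which the drug acts; the text also allows the reading of a latest enrolment time, and the article should say which it intends.

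On either reading, the trial estimates the average effect of HDIVC started within 7 days of onset in patients who already have persistent organ failure. That estimate is valid. The weakness is that the named strata, primary model and sensitivity analyses leave out a variable that the rationale treats as decisive and that eligibility already establishes. This is a worthwhile improvement to the stated analysis and its wording, and it does not invalidate the design.

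**What to change.** 1. Reconcile Inclusion criteria, Intervention and the Discussion on what the 7-day window means. This concerns wording; no change to treatment is proposed here.
2. Add time from onset to randomisation, as a continuous variable, to the OSFD model as a prespecified covariate.
3. Name treatment by time from onset among the subgroup interaction tests. Report it as supportive and non-confirmatory, with confidence intervals.
4. Adjust the Day 7 CRP comparison for baseline CRP and time from onset. Table 1 already schedules the Day 0 value.
5. Describe the objective as HDIVC started within 7 days of onset in patients with persistent organ failure. If the first infusion can wait for the next 06:00 cycle, say enrolled instead of started.

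Use of the word *early* should not depend on the interaction result. A benefit that is uniform across the window would show no interaction, and the estimate will be imprecise in any case.

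The cost is text and analysis specification, with no new data and no change to N. The downside is the low precision of the interaction at N = 238. With 34 of 238 patients (14%) reported as recruited and the interim planned at about 50%, prespecification would still be credible. If an analysis plan not shown already contains items 2 to 4, only the wording changes remain.

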## Glossary

ICU: Intensive care unit
SAP: Severe acute pancreatitis
HDIVC: High-dose intravenous vitamin C
AP: Acute pancreatitis
ROS: Reactive oxygen species
SIRS: Systemic inflammatory response syndrome
MODS: Multiple organ dysfunction syndrome
ARDS: Acute respiratory distress syndrome
COVID-19: Coronavirus disease 2019
RNS: Reactive nitrogen species
ACTH: Adrenocorticotropic hormone
NF-κB: Nuclear factor-kappa B
MSAP: Moderately severe acute pancreatitis
CRP: C-reactive protein
OSFD: Organ support-free days
ERCP: Endoscopic retrograde cholangiopancreatography
eGFR: Estimated glomerular filtration rate
AIDS: Acquired Immunodeficiency syndrome
IL-6/IL-1/IL-10: Interleukin-6/interleukin-1/interleukin-10
SOFA: Sequential organ failure assessment
APACHE II: Acute physiology and chronic health evaluation II
BISAP: Bedside index for severity in acute pancreatitis
CTSI: Computed tomography severity index
IPN: Infected pancreatic necrosis
UDPN: Unblinded drug preparation nurse
KDIGO: Kidney disease: improving global outcomes
GCP: Good clinical practice
PI: Principal investigator
IRB: Institutional review board
MICE: Multiple imputation by chained equations
LOCF: Last observation carried forward
ITT: Intention-to-treat
PP: Per-protocol
DMC: Data monitoring committee
AE: Adverse event
SAE: Serious adverse event
NT-proBNP: N-terminal pro-B-type natriuretic peptide
TnI: Troponin I
CT: Computed tomography
